### Interventions

This is a protocol for a double-blind, randomized, parallel-group, placebo-controlled, monocenter trial in patients with OCD. The trial will include 1 active memantine dose arm and 1 placebo arm.

The trial will consist of the following four distinct periods:

Screening: the screening period may last up to 4 weeks for each eligible patient.A 32-week, double-blind, up-titration treatment period (from T0 to T4): after screening, patients who meet all eligibility criteria will be randomly assigned to 1 of 2 arms (memantine or placebo) in a 1:1 ratio. Following baseline assessments, each patient will receive a daily dose of memantine or the placebo (up to 20 mg/day).An 8-week, double-blind, down-titration treatment period (from T4 to T5): at T4, the dose of memantine or the placebo will be reduced to 10 mg per day due to safety reasons, before the end of treatment (T5).Follow-up period (from T5 to T6): after the 40-week, double-blind treatment period, patients will be asked to come back for the follow-up visit (T6) 8 weeks after the end of the treatment (T5; Figures 2 and 3).

**Figure 2 figure2:**
[figure not shown]
Study Flow-chart.

**Figure 3 figure3:**

Study Timeline.

### Recording of Adverse Events

The investigator will carefully monitor the patients’ symptoms and signs, which will be either spontaneously reported or detected, throughout the whole study period up to the last visit scheduled in the study protocol. On a case-by-case basis, a prolonged observation period may be requested.

Adverse events that occur during the clinical trial will be assessed by the investigator in terms of their seriousness and relationship with the investigational product, and the principal investigator will be notified.

As soon as a severe adverse event occurs, an ad hoc form for severe adverse events will be completed, in accordance with the European Union regulation about pharmacovigilance in clinical research [52]. If, for any reason, the disadvantages of participation appear to be significantly greater than those foreseen, the investigator will inform the principal investigator and the bodies providing ethical oversight to evaluate trial discontinuation for the patient.

### Sample Size

The sample size was calculated by using the G*Power 3.1.9.2 software (Heinrich-Heine-Universität Düsseldorf) [53]. By using the ANOVA repeated measures test with a within-between group interaction approach (considering changes in Y-BOCS scores as the primary outcome), an α of .5, a power (1 − β) of 0.85, 2 groups (SSRI and memantine group vs SSRI and placebo group), and 7 measurements (T0 to T6); and by assuming a correlation of 0.5 among repeated measures and a nonsphericity correction ε of 1, we determined that a total sample size of 20 participants (10 in each group) will be necessary to achieve a moderate effect size (*f*=0.25).

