### Statistical Methods

Descriptive statistics for baseline characteristics and the measurements at each time point will be calculated. For the primary objective, a repeated measures ANOVA approach will be used to detect between- and within-group differences in Y-BOCS variables. *P* values of <.05 will be considered statistically significant. Data will be analyzed by using SPSS version 20 (IBM Corp).

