### Limitations

Our outpatient clinic—a center specializing in OCD—is an academic service of the Department of Human Neurosciences, Sapienza University of Rome. This could represent a limitation—patient selection bias—due to patients’ access to the center’s services. Moreover, our study will use a small sample size due to the limits of service access and the inclusion criteria.

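### The f=0.25 behind N=20 is labelled moderate, but on the scale that yields 20 patients it needs a peak memantine-placebo difference of about 1.0 to 1.6 SD

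*Protocol article*

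**What the plan says.** The Sample Size section of the protocol article bases the calculation on an "ANOVA repeated measures test with a within-between group interaction approach", with "2 groups (SSRI and memantine group vs SSRI and placebo group"), "7 measurements (T0 to T6"), "a power (1 − β) of 0.85", and "assuming a correlation of 0.5 among repeated measures and a nonsphericity correction ε of 1". It concludes that "a total sample size of 20 participants (10 in each group) will be necessary to achieve a moderate effect size", given as f=0.25. Alpha is printed there as .5, whereas under Statistical Methods P "values of <.05 will be considered statistically significant".

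The outcome is change in Y-BOCS score. The section does not translate f into a treatment difference and does not say which of the software's effect-size options was used. The Limitations section adds that "our study will use a small sample size due to the limits of service access and the inclusion criteria", a reason that has nothing to do with the effect size.

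**The concern.** In a plain comparison of two group means, f=0.25 corresponds to a difference of 0.5 SD, and that is what a reader will take a moderate effect to mean. In the within-between interaction the same symbol measures something else: how much the group difference varies from visit to visit. A given f can then correspond to a much larger difference between the arms at any one visit.

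What is at stake is how the result is read. A reader who accepts the stated basis will think the trial has 85% power for a moderate benefit, and may take P above .05 as evidence against one. If the true peak difference is 0.5 SD, the trial would usually miss it.

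**Working it through.** **Inputs.** From Sample Size: k=2 groups, m=7 measurements, rho=0.5, epsilon=1, f=0.25, power 0.85, N=20. From Statistical Methods: alpha 0.05. Allocation is 1:1 (Interventions).

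**1. Reproduce N=20.** On the default scale the noncentrality is lambda = f²·N·m·epsilon/(1−rho), with df1=(k−1)(m−1)=6 and df2=(N−k)(m−1).

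- N=20: lambda = 0.0625 × 20 × 7/0.5 = 17.5, df 6 and 108, power 0.881.
- N=18: lambda = 15.75, df 6 and 96, power 0.836.

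So 20 is the smallest even total that reaches 0.85. Other readings do not give 20: the printed alpha of .5 gives 8 on this scale, and at alpha 0.05 the same software's Cohen and SPSS effect-size options give 42 and 44.

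**2. What f means on this scale.** Let d(t) be the memantine-placebo difference at visit t and sigma the between-patient SD at one visit. With two equal groups each interaction term is ±(d(t) − mean of d)/2, so

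f = SD over visits of d(t) / (2·sigma).

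Hence f=0.25 requires d(t) to vary over the seven visits with an SD of 0.5 sigma. With rho=0.5 the SD of change from baseline is sigma·√(2(1−0.5)) = sigma, so the same figures hold for change scores.

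**3. Convert to a peak difference.** Take d(T0)=0 and a peak of D, and let s be the SD over visits of the pattern scaled to a peak of 1. Then D = 0.5/s. For power at a given D, use f = D·s/2 in step 1 with N=20 and alpha 0.05.

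| Pattern of the difference, T0 to T6 | s | Peak for f=0.25 | Power, peak 0.5 SD | Power, peak 0.8 SD |
|---|---|---|---|---|
| Step, present T3–T6 only or T1–T4 only | 0.495 | 1.01 SD | 0.273 | 0.662 |
| Step, present T2–T6 or T1–T5 | 0.452 | 1.11 SD | 0.229 | 0.568 |
| Ramp to T4, then held | 0.375 | 1.33 SD | 0.165 | 0.399 |
| Immediate, sustained T1–T6 | 0.350 | 1.43 SD | 0.148 | 0.348 |
| Ramp to T4, half at T5, none at T6 | 0.346 | 1.44 SD | 0.145 | 0.341 |
| Linear T0–T6 | 0.333 | 1.50 SD | 0.137 | 0.316 |
| Ramp to T5, half at T6 | 0.316 | 1.58 SD | 0.127 | 0.285 |
| Ramp to T4, then 0.75 and 0.5 of peak | 0.311 | 1.61 SD | 0.124 | 0.276 |

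Example, linear pattern with a 0.5 SD peak: f = 0.5 × 0.333/2 = 0.083, lambda = 0.083² × 20 × 14 = 1.94, power 0.137.

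**4. Lower bound.** With d(T0)=0 and all values between 0 and D, the variance over seven visits is largest when three or four visits sit at D and the rest at 0: (3/7)(4/7)D² = 12D²/49, so s=0.495. No one-sign pattern starting at zero needs less than 0.5/0.495 = 1.01 SD.

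**5. Exactly 85% power.** Because N=20 gives 0.881 at f=0.25, power of 0.85 is reached at f=0.240. The peak range then becomes 2 × 0.240/0.495 = 0.97 SD to 2 × 0.240/0.311 = 1.54 SD.

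**6. Checks.** Simulation (20,000 runs per scenario) at f=0.25 gave power of 0.88 for the linear, immediate and T3–T6 step patterns. At a 0.5 SD peak it gave 0.14, 0.15 and 0.27. A single-visit comparison with 10 per arm and a 0.5 SD difference has power of about 0.19 by t test, or 0.23 with baseline adjustment at rho=0.5. The low power is therefore not peculiar to the interaction test. For 85% power at a 0.5 SD peak the interaction test would need a total of 74 to 182 patients, depending on pattern.

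**The case against.** The strongest reply is that nothing has been miscalculated. The section names the test, f, the correlation, epsilon and the number of measurements, and with alpha at 0.05 the design does have at least 85% power for the f entered. It never equates f=0.25 with a 0.5 SD difference in Y-BOCS. This stands. A reader might infer that the sample size is arithmetically wrong, or that the trial lacks the power claimed for its stated f; the document supports neither. What remains is the label, and it matters because it is the only description of the effect's size in words.

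A second reply is that the size depends on a time pattern the article does not give. This also stands. Gradual patterns may seem natural, since the dose is raised from T0 to T4, reduced to T5 and stopped before T6. A reader who uses only ramps would quote power of 0.12 to 0.17 at 0.5 SD and 0.28 to 0.40 at 0.8 SD. But the article predicts no pattern and treats the minimum effective dose and residual efficacy as things to be observed. The step patterns belong in the range, and they raise the upper ends to 0.27 and 0.66.

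Third, 1.01 SD is not an absolute floor. If the difference could reverse sign the bound would be lower: equal and opposite differences over T1–T3 and T4–T6 give s=√(6/7)=0.926 and a peak of 0.54 SD. Such a reversal is implausible here, but the one-sign condition has to be stated.

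Fourth, the article admits a small sample. That disclosure is not an error, but it does not withdraw the description of the detectable effect. The absence of an SD or a difference in Y-BOCS points is a detail that an article may leave to the full protocol, and I do not count it against the plan.

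**Conclusion.** The point holds as a mislabelled effect size. On the scale that gives 20 patients, f=0.25 is a peak between-group difference of 1.01 to about 1.6 SD, which is two to three times the 0.5 SD that moderate usually denotes between two groups. A true peak difference of 0.5 SD would be missed about 73% to 88% of the time. Even at 0.8 SD, power stays below 0.85 under every pattern tried.

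These figures assume alpha 0.05, no difference at T0, a difference that keeps one sign, a common SD, rho=0.5 and epsilon=1 as the article assumes, and all 20 patients contributing. The spread within each range comes from the unknown time pattern. The sizes are left in SD units because the article gives no Y-BOCS SD; any conversion to points would rest on an assumed one. The printed alpha of .5 is a separate error and does not explain the figure of 20.

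**What to change.** In the Sample Size section, delete the word moderate. State instead that 20 patients give 85% power, under the planned interaction test, only for a peak memantine-placebo difference of roughly 1.0 to 1.6 SD in Y-BOCS. Name the time pattern assumed, the software's effect-size option and alpha 0.05; once one pattern is chosen, the range becomes a single figure from the table. Add a sentence that a non-significant result will not be read as excluding a 0.5 SD benefit.

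The detectable effect should be stated for the repeated measures ANOVA that Statistical Methods plans. A figure for a baseline-adjusted contrast at T4 would describe a different analysis, and the article does not make T4 the primary time point.

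The change is to wording only and adds no patients. Its cost is a less favourable stated detectable effect.

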### Randomization and Blinding

Placebo and memantine tablets will be identical in shape, color, weight, and scent. We will prepare in advance a computer-generated random number sequence for random group assignment. Treatment allocation will be concealed from the patients, from the physicians rating the patients, and from the statistician. Separate individuals will be responsible for randomization and the rating of patients.

### Data Collection and Quality Control

Patients will be enrolled after the physician in charge and a supervisor check the patient information regarding the inclusion and exclusion criteria. The data of all participants, including those who are discontinued or dropped from intervention protocols, will be collected according to the study protocol. Quality control will be performed by an external data manager (recruited exclusively for this project).

### Statistical Methods

Descriptive statistics for baseline characteristics and the measurements at each time point will be calculated. For the primary objective, a repeated measures ANOVA approach will be used to detect between- and within-group differences in Y-BOCS variables. *P* values of <.05 will be considered statistically significant. Data will be analyzed by using SPSS version 20 (IBM Corp).

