### Trial Design

A double-blind, randomized, parallel-group, placebo-controlled, monocenter trial will be conducted over 52 weeks at the outpatient clinic of the Department of Human Neurosciences, Sapienza University of Rome. The study population will include patients diagnosed with moderate to severe OCD according to the diagnostic criteria of the DSM-5 who consecutively access the OCD outpatient clinic of the Department of Human Neurosciences, Sapienza University of Rome. The investigators will be academic research assistants and psychiatrists with experience in OCD.

We will enroll patients who meet the diagnostic criteria of the DSM-5 [12] for moderate to severe OCD, and those with a Yale-Brown Obsessive Compulsive Scale (Y-BOCS) [42] score of >21 will be selected for inclusion in the study. The Y-BOCS, which will be used to evaluate treatment efficacy, is a well-validated, 10-item rating scale that is widely used to measure the severity of OCD symptoms. Participants will be rated with the Y-BOCS at baseline and at 2, 4, 6, 8, 10, and 12 months.

During the screening period and T4 and T6 follow-up visits, all participants will undergo an extensive neuropsychological evaluation. We will assess processing speed by using the Wechsler Adult Intelligence Scale, Fourth Edition, Digit Span [43]; attention by means of the Trial Making Test [44]; computerized alertness and go/no-go task memory by using the Digit and Corsi Span [45], a modified version of the Corsi Block-Tapping Test [46], the story recall portion of the Rivermead Behavioral Memory Test [47], and a modified version of the Babcock Story Recall Test [48]; and executive functions by means of the Stroop task [49], a modified version of the Tower of London test [50], and the Modified Five-Point Test [51].

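### The primary repeated measures ANOVA spans the reduced-dose visit T5 and the off-drug visit T6, so it does not isolate memantine's benefit on treatment

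*Protocol article*

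**What the plan says.** The main aim (Introduction, Objectives) is the efficacy and safety of memantine added to an SSRI.

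- **Statistical Methods:** for the primary objective, "a repeated measures ANOVA approach will be used to detect between- and within-group differences in Y-BOCS variables". No visit, contrast or interaction is named.
- **Sample Size:** the calculation uses an "ANOVA repeated measures test with a within-between group interaction approach (considering changes in Y-BOCS scores as the primary outcome") and "7 measurements (T0 to T6").
- **Trial Design:** "Participants will be rated with the Y-BOCS at baseline and at 2, 4, 6, 8, 10, and 12 months", which gives the seven visits.
- **Interventions:** the first phase is "A 32-week, double-blind, up-titration treatment period (from T0 to T4"). Then "at T4, the dose of memantine or the placebo will be reduced to 10 mg per day due to safety reasons", and this phase ends with treatment at T5. Finally, "patients will be asked to come back for the follow-up visit (T6) 8 weeks after the end of the treatment".
- **Abstract (Results) and Conclusion:** the follow-up after T5 is there to show whether any effect remains after withdrawal.

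**The concern.** A primary test of efficacy should be significant when memantine beats placebo during treatment, and should rarely be significant otherwise. A repeated measures ANOVA over T0 to T6 offers three effects, and none of them is that comparison.

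- **Group-by-time interaction (the effect powered).** It asks whether the arm difference varies in any way over seven visits. It has 6 degrees of freedom and no direction. Arms that separate only after dose reduction or withdrawal satisfy it as well as arms that separate on treatment.
- **Between-group main effect.** It averages the arm difference over all visits, including T0 before any dose and T6 off drug.
- **Within-group change.** It does not compare the arms, and placebo patients can change too.

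A significant primary result could therefore be reported without benefit at any visit up to T4. Even a genuine result would not show in which phase it arose.

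**Working it through.** **Inputs from Sample Size:** N = 20 (10 per arm), m = 7 visits, correlation ρ = 0.5, ε = 1, f = 0.25, target power 0.85. I use α = .05, as in Statistical Methods. The .5 printed under Sample Size would give N = 8, not 20.

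**1. The plan's own figure.** For the interaction, λ = f²·N·m/(1 − ρ), df1 = m − 1, df2 = (N − 2)(m − 1).

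- N = 20: λ = 0.0625 × 20 × 7/0.5 = 17.5, df 6 and 108, power 0.881.
- N = 18: λ = 15.75, df 6 and 96, power 0.836, below 0.85.

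So 20 is reproduced as the seven-visit interaction. With T0 to T4 only (m = 5) and the same f, N = 20 gives power 0.79, and 24 patients are needed. T5 and T6 are thus built into the published sample size.

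**2. Arms that differ only after T4.** The documents give no SD or expected difference, so the profiles below are assumptions, in SD units, with equal correlations of 0.5. For a profile d of arm differences, λ = N·Σ(d − d̄)²/[4(1 − ρ)] = 10·Σ(d − d̄)² at N = 20. Take d = (0, 0, 0, 0, 0, D/2, D), for which Σ(d − d̄)² = 0.9286·D².

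| D at T6 | λ | Probability that the interaction is significant |
|---|---|---|
| 0.5 SD | 2.32 | 0.16 |
| 0.8 SD | 5.94 | 0.38 |
| 1.0 SD | 9.29 | 0.58 |
| 1.4 SD | 18.2 | 0.90 |

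The design value f = 0.25 corresponds to Σ(d − d̄)² = 0.0625 × 28 = 1.75. This post-T4 profile reaches that at D = √(1.75/0.9286) = 1.37 SD. The effect size in the plan therefore does not say whether the separation occurs on or off treatment.

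**3. A real benefit of 1 SD at T4.**

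- Interaction, linear build-up to T4, half left at T5 and none at T6 (0, .25, .5, .75, 1, .5, 0): λ = 8.39, power 0.53.
- Interaction, same build-up, sustained at T5 and T6: λ = 9.82, power 0.60.
- Unadjusted change from T0 to T4: SD of change = √(2 × 0.5) = 1, SE = √(4/20) = 0.447, df 18, power 0.56.
- Baseline-adjusted difference at T4: SE = √(0.75 × 0.2) = 0.387, df 17, power 0.68.
- Between-group main effect, fading profile: mean difference 3/7 = 0.43 SD, λ = (20/4) × 0.43²/(4/7) = 1.61, df 1 and 18, power 0.22.

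**4. Design figure for the T4 contrast.** With 10 per arm and baseline adjustment, power is 0.23 at 0.5 SD, 0.50 at 0.8 SD and 0.68 at 1.0 SD. It reaches 0.85 at 1.23 SD.

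**The case against.** The seven-visit set is a sample-size input, and Statistical Methods names no visits. Its wording may be loose shorthand for the same mixed ANOVA, and a fuller analysis plan may hold planned contrasts. This stands in part: the visit set has to be inferred from two sections. But the article's only sample size rests on T0 to T6, and a later plan could not drop T5 and T6 and keep that figure.

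The power comparison can also be made to flatter the fix. The gain from 0.53 to 0.68 is mostly baseline adjustment, since the unadjusted T4 test has 0.56. If the benefit persists to T6, the interaction has 0.60. This stands, and it is why lost power is not the main charge. The 90% figure needs a 1.4 SD difference that no document states, so it belongs in a range.

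A reader might go further in three ways that the documents do not support.

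- **That the test does not test on-treatment benefit at all.** It does respond to separation during treatment; it does not isolate it.
- **That T6 is unblinded because the 40 treatment weeks are the part labelled double-blind.** Trial Design calls the whole 52-week trial double-blind, and Randomization and Blinding sets no end to concealment.
- **That power is really 0.29, or that 86 patients are needed.** Those figures apply f = 0.25 to the between-group main effect. The plan powers the interaction, and the same f is a different treatment difference there, so they show no shortfall in the stated power.

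**Conclusion.** The concern holds as a lack of specificity and direction. The primary test that emerges from Sample Size and Statistical Methods includes a reduced-dose visit and an off-drug visit, and no on-treatment memantine-placebo contrast is named. With no difference up to T4, it would be significant in about 38% to 90% of trials for an assumed T6 difference of 0.8 to 1.4 SD, half of it present at T5. For a true 1 SD benefit at T4 its power (0.53 to 0.60) is close to that of an unadjusted T4 comparison (0.56) and below that of a baseline-adjusted one (0.68). All of this assumes N = 20 with complete data, α = .05, equal correlations of 0.5 and the profiles shown. T5 still lies within the treatment period, at a reduced dose; only T6 is off drug.

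**What to change.** Name one primary test: the memantine-placebo difference in Y-BOCS total at T4, the last visit before dose reduction, adjusted for baseline, two-sided at .05. Make T5 and T6 separate secondary contrasts, with T6 answering the residual-efficacy question. Report within-group changes descriptively only. Restate the sample-size section for the T4 contrast, with its assumed difference, SD and correlation.

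No visit, dose or measurement changes, but this is more than a wording change. The stated power becomes less favourable: at ρ = 0.5, 85% power for 0.8 SD needs 46 patients in total and for 1.0 SD needs 30. If N stays at 20, the article should say that it has 85% power only for about 1.23 SD.

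There is also a pattern in which the interaction would do better. If a 1 SD effect is full by T1, halves at T5 and is gone at T6, its power is 0.77 against 0.68 for the T4 contrast. Part of that advantage comes from the withdrawal phase, which is a separate question.

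### The primary repeated measures ANOVA by default needs all seven Y-BOCS ratings and leaves baseline unadjusted; the 20-patient total states no dropout allowance, and a mixed model would use the data better

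*Protocol article*

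**What the plan says.** The Statistical Methods section gives the primary analysis in one sentence: "a repeated measures ANOVA approach will be used to detect between- and within-group differences in Y-BOCS variables". The software is SPSS version 20, and P "values of <.05 will be considered statistically significant".

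The Sample Size section uses the same family of test: "By using the ANOVA repeated measures test with a within-between group interaction approach (considering changes in Y-BOCS scores as the primary outcome"), with "7 measurements (T0 to T6"), correlation 0.5 among the measurements, nonsphericity correction 1 and f = 0.25. The result is that "we determined that a total sample size of 20 participants (10 in each group) will be necessary to achieve a moderate effect size". No allowance for dropout is mentioned. This section also prints "an α of .5, a power (1 − β) of 0.85"; that alpha conflicts with the .05 of Statistical Methods.

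The Data Collection and Quality Control section adds: "The data of all participants, including those who are discontinued or dropped from intervention protocols, will be collected according to the study protocol". The article does not say how those data enter the primary analysis.

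Under Interventions, T0 to T4 takes 32 weeks, T4 to T5 takes 8, and T6 follows 8 weeks after treatment ends.

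**The concern.** Classical repeated measures ANOVA needs a value at every level of the time factor. Unless something else is specified, a patient with six of seven ratings contributes nothing. T6 is an off-drug visit, so someone with every on-treatment rating who misses only that visit would leave the primary efficacy test. Ratings gathered from patients who stop treatment would be lost in the same way whenever one rating is absent.

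Three things are at stake:

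- **Power.** The calculation treats all 20 patients as complete, and small miss rates compound over six follow-up visits.
- **Bias.** If patients leave for reasons tied to tolerability or lack of benefit, and these differ by arm, the completers are no longer the groups that were randomised. Enrolling more patients would not cure that.
- **Precision.** Baseline Y-BOCS is collected from everyone, but it is used as a level of the outcome and not to reduce residual variance.

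**Working it through.** **Inputs (Sample Size section):** k = 2 groups, m = 7 measurements, f = 0.25, rho = 0.5, epsilon = 1, target power 0.85. Alpha is taken as .05 from Statistical Methods.

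**Formula (within-between interaction, noncentral F):** lambda = f² × N × m / (1 − rho), df1 = (k − 1)(m − 1) = 6, df2 = (N − k)(m − 1) = 6(N − 2).

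**Reproducing the plan's figure.** At N = 20, lambda = 0.0625 × 20 × 7 / 0.5 = 17.5 with df 6 and 108, and power is 0.881. At 18 (9 + 9) power is 0.836, below target, so 20 is the smallest balanced total. The printed alpha of .5 would instead give 8. The stated 20 thus fits .05 and not .5.

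**Power by number of complete patients (same formula, alpha .05):**

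| Complete | lambda | df2 | Power |
|---|---|---|---|
| 20 | 17.500 | 108 | 0.881 |
| 19 | 16.625 | 102 | 0.860 |
| 18 | 15.750 | 96 | 0.836 |
| 17 | 14.875 | 90 | 0.809 |
| 16 | 14.000 | 84 | 0.778 |
| 15 | 13.125 | 78 | 0.743 |
| 14 | 12.250 | 72 | 0.705 |

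If both losses fall in one arm (10 + 8), N in lambda is replaced by 4 × 10 × 8 / 18 = 17.8, and power is 0.831.

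**Compounding over visits.** T0 to T6 spans 32 + 8 + 8 = 48 weeks with six follow-up ratings. The article gives no miss rate, so a rate q per visit is assumed, independent across visits. The chance of a complete record is (1 − q)^6, and the number complete is binomial with 20 trials. Mean power averages the formula over that distribution.

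| q (assumed) | (1 − q)^6 | Expected complete | Chance of 18 or fewer | Mean power |
|---|---|---|---|---|
| 2% | 0.886 | 17.7 | 68% | 0.83 |
| 5% | 0.735 | 14.7 | 98% | 0.72 |
| 10% | 0.531 | 10.6 | over 99% | 0.54 |

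These means treat the completers as evenly split. Allowing for chance imbalance between arms lowers them to 0.82, 0.71 and 0.51 or 0.52.

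**Baseline.** For an arm contrast at a single follow-up visit with equal variances, the variance relative to one rating is 2(1 − rho) = 1.00 for a change score and 1 − rho² = 0.75 with baseline as covariate. At the plan's rho = 0.5 that is a 25% reduction.

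**The case against.** **Complete-case deletion is not written anywhere.** A reader might infer that the plan excludes anyone who misses a visit. The article does not say so. It names the method and is silent on missing ratings, which may be handled in a full protocol or SAP that is not shown. This stands as a limit on wording: deletion is the default of the named method, not a declared rule. It does not remove the point, because the choice of method is stated and a better one is available in the same software.

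**Stopping treatment is not a missing rating.** A patient who discontinues but attends every visit has seven scores and stays in the ANOVA. That is right. The commitment to collect data after discontinuation helps, and only patients who also miss a rating are lost.

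**The power loss can be overstated.** A reader might infer that two dropouts destroy the stated power, or that there is no margin at all. Neither holds. Rounding up to a balanced total leaves room for one loss (0.860 at 19), and two losses fall only 1.4 to 1.9 percentage points short of 0.85.

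**Baseline as a level is valid.** Under randomisation the group-by-time interaction is a legitimate test with T0 included, so this is a matter of efficiency. It might be inferred that adjustment makes 20 patients worth 20 / 0.75, about 27. That ratio belongs to a single-visit contrast and does not carry over to the 6-df interaction.

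**A mixed model can also be overfitted.** Six post-baseline visits under an unstructured covariance need 6 × 7 / 2 = 21 variance and covariance parameters from 20 patients. That is fragile and must shape the remedy.

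**Conclusion.** The concern holds as a poor choice of analysis combined with a sample size that states no dropout allowance. It does not show an invalid test or a stated exclusion rule.

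Under the method's default, power is near target with one or two incomplete patients, 0.78 with four and 0.70 with six. With assumed independent miss rates of 2% to 5% per visit, mean power is about 0.83 to 0.72. Falling to 18 or fewer complete records is then the likelier outcome, with a chance of 68% to 98%.

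These figures rest on alpha .05, the plan's own f, rho and epsilon, and complete-case handling. The miss rates are illustrations, since the article gives none. The risk of bias is real if missing ratings relate to tolerability or response, but its size cannot be calculated from the article.

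**What to change.** 1. **Replace the repeated measures ANOVA with a linear mixed model** (SPSS MIXED, REML). The outcome is Y-BOCS at T1 onward. The fixed effects are treatment, visit, treatment-by-visit and baseline Y-BOCS.
2. **Include every randomised patient with at least one post-baseline rating**, and keep ratings taken after treatment stops.
3. **Prespecify a parsimonious covariance structure** suited to 20 patients, instead of relying on an unstructured matrix.
4. **Restate power for an assumed number of complete patients**, for example 0.78 with 16 under the current method, and reconcile the printed alpha of .5 with .05.

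The cost is revised wording and slightly more analysis work in software already named. The model relies on data being missing at random and on a simpler covariance structure, and the stated power will look less favourable. According to the Results section recruitment had not begun at publication, so at that stage the change could be made before any outcome data existed.
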